### Intervention

All adolescents and their parents (both the control group and the intervention group) will receive insulin pump standard start training, including technical skills and how to use carbohydrate counting with CSII. The parents will simulate diabetes by wearing a pump containing saline and test their blood glucose before the child starts insulin pump treatment. The education intervention will be conducted in connection with starting CSII (on three occasions) and on four occasions in the first 4 months after starting CSII. Each session will last 1.5-2 hours. The intervention will be performed by two diabetes nurses (Figure 1). The GSD-Y method will be used with structured reflection sheets. The first reflection sheet will be sent to participants before their first appointment. For subsequent appointments, the reflection sheet for the next meeting will be distributed at that appointment and completed before the next appointment. By filling in the reflection sheet using their own words and drawings, adolescents and their parents systematically explore and express their own experiences and difficulties with diabetes in daily life (Table 1). In the dialogue, different communication models are used, including mirroring, active listening and value-clarifying responses [30,31]. Three diabetes nurses and two dieticians have been trained to use GSD. Together with the creators of GSD and GSD-Y ([name] and [name]) [30,31], we have adjusted GSD-Y so that it fits this study. The worksheets have been translated into Swedish and retranslated by a Danish and Swedish speaking person.

**Figure 1 F1:**
[figure not shown]
Flow chart of the study.

**Table 1 T1:** Overview of reflection sheets

Visit 1 (Start CSII)	**Your life with diabetes from the beginning to now**
	• Written invitation to work together in a new way
	• Two ways of looking at HbA1c
	• Agreement on things to work on
Visit 2 (Start CSII)	**Your life with diabetes from the beginning to now**
	• Important events and periods in your life
	• What do you find difficult at present living with your diabetes?
	• Your plans for changing your way of life
Visit 3 (Start CSII)	**Values and opportunities**
	• Unfinished sentences: needs, values, experiences and opportunities?
Visit 4	**Diabetes in your life**
	• A picture or expression describing your life with diabetes
	• Room for diabetes in your life
	• Shared responsibility between adolescent and parent for diabetes in daily life
	• Common name for a difficulty in your life with diabetes
	• Agreement on things to work on until next visit
Visit 5	**Problem identification and problem solving**
	• Current problem solving
	• Dynamic problem solving
	• Agreement on things to work on until next visit
Visit 6	**Different ways of looking at numbers**
	• Blood glucose (BG) tests and your reasons for checking
	• Actual BG numbers and wishes
	• Your plan for BG regulation in the short and long run.
	• Common name for a difficulty in your life with diabetes
	• Agreement on things to work on until next visit
Visit 7	**Problem identification and problem solving**
	• Current problem solving
	• Dynamic problem solving
	• Solved problems and subjects to continue working on

### Measures and data collection

The data to be collected during this study is shown in Table 2. HbA1c levels will be assessed using a capillary test and analysed using the DCA 2000 apparatus (Siemens Medical Solution Diagnostics, Mölndal, Sweden). Normal reference for children between 6 months and 18 years is 31-38.6 mmol/mol [32]. The mean frequency of bolus doses and percentage doses using carbohydrate counting from the last 2 weeks will be used. The following instruments will be used to evaluate perceived health and QoL: Disabkids, ‘Check your health’, the Diabetes Family Conflict Scale (DFCS) and the Swedish Diabetes Empowerment Scale (Swe-DES 23). Disabkids measures the generic health of children with chronic illnesses and has a specific diabetes module. The Disabkids test has good reliability and validity [33]. ‘Check your health’ measures perceived physical and emotional health, social relationships and general QoL on vertical thermometer scales, ranging from 0 to 100, with 0 indicating low perceived health and QoL. Using the same scales, a person reports what their perceived physical and emotional health, social relationships and QoL would be if they did not have diabetes. The measured difference between, for example, physical health with and without diabetes is defined as the physical burden of diabetes. When the difference results in a positive value, meaning that, for example, imagined physical health without diabetes is reported to be lower than with diabetes, the burden is interpreted as zero. In this study, the marginal values for no burden, low burden, high burden or very high burden will be arbitrary. ‘Check your health’ has been tested on adolescents and adults with diabetes and has shown good reliability and validity [34,35], and it is being validated on parents to young persons with type 1 diabetes. DFCS is the most widely used measure of diabetes-specific family conflicts and has recently been modified [36]. It has been translated and validated on young persons with type 1 diabetes [37]. Swe-DES 23 measures the psychosocial self-efficacy of people with diabetes and has been validated in Swedish for adults. The SWE-DES-23 has four empowerment subscales: goal achievement (alfa: 0.91), self-awareness (alfa: 0.80), stress management (alfa: 0.80), and readiness to change (alfa: 0.68). Cronbach’s alfa-coefficient for the total score was found to be 0.91, demonstrating acceptable reliability and validity [38]. Treatment satisfaction will be measured with one question.

**Table 2 T2:** Data collection

**Before starting CSII**	• HbA1c, height, weight, insulin requirement, mean frequency of self-monitoring of blood glucose (SMBG)
	• ‘Check your health’, Disabkids, DFCS, Swe-DES 23 and treatment satisfaction.
**6 and 12 months after starting CSII**	• Same measures as before starting CSII
	• Frequency of bolus doses and usage of carbohydrate counting

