**Methods/design:**

This study is designed as a randomized, controlled, prospective, multicentre study. Eighty patients between 12–18 years of age who are planning to start CSII will be included. All adolescents and their parents will receive standard insulin pump training. The education intervention will be conducted when CSII is to be started and at four appointments in the first 4 months after starting CSII. The primary outcome is haemoglobin A1c levels. Secondary outcomes are perceived health and QoL, frequency of blood glucose self-monitoring and bolus doses, and usage of carbohydrate counting. The following instruments will be used: Disabkids, ‘Check your health’, the Diabetes Family Conflict Scale and the Swedish Diabetes Empowerment Scale. Outcomes will be evaluated within and between groups by comparing data at baseline, and at 6 and 12 months after starting treatment.

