### Statistical analysis and power calculation

To detect a difference of 6 mmol/mol in HbA1c (SD: ± 9.1), at least 37 participants are required in each group (power 80% and alpha 0.05). SD is calculated from the available participants in the actual clinics (n = 160) at study start, mean HbA1c: 74.2 ± 9.1 mmol/mol. Allowing for patient withdrawals and those lost to follow up, 80 patients will be included in the study. All analysis will be conducted on an intention-to-treat basis. The differences between the groups will be analysed using an un-paired t-test with a 95% confidence interval and p < 0.05 considered as significant. A repeated measures ANOVA will be used for before and after comparisons in the groups, using the same confidence interval and level of significance. When testing differences between groups using Disabkids, ‘Check your health’, DFCS and Swe-DES 23, the same statistical analysis will be used.

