## Discussion

The aim of our study is to provide an educational program in an urban area, and its success depends on how well the study participants represent the population of interest. Previous studies have indicated that children with many diabetes-related conflicts have poorer glycaemic control, and thus, it is important that this group be represented in the study sample [27]. We have chosen to use HbA1c measured at the visit before the planned start of CSII as the inclusion criterion. An alternative, which is common in studies with adults, is to use a mean result from three HbA1c tests taken in the last year. We did not use this latter method as part of the entry criteria because some of the potential patients will have been diagnosed with diabetes for only a short time, and there is a risk of using an HbA1c result from a remission period. GSD is an empowerment-based program, and we have thus chosen to use Swe-DES 23, which is sensitive to change. Previous studies show that unclear responsibility distribution can explain omitted bolus doses and family conflicts, and we will also use DFCS, which is one of the most widely used measures of diabetes-specific family conflict [21,27]. To detect changes in perceived physical and emotional health, social relationships, general QoL and the burden of diabetes, we will use the measures Disabkids and ‘Check your health’ [33-35]. There is a risk that there will be high scores on perceived QoL already at baseline, but it is important to detect both rates of deterioration and improvement. We also want to observe any changes in the burden of diabetes. We will measure treatment satisfaction with one question; we have used this question in previous studies and it has been shown to be sufficient for measuring treatment satisfaction [18]. The intervention will take 4 months and evaluation with measurements of perceived QoL will be performed at baseline, 6 and 12 months to allow comparisons and to determine any changes. Previous research has shown that there is an initial improvement in the first months after the start of treatment using an insulin pump, which later subsides [14,16]. We believe that starting an insulin pump together with an empowerment-based, person-centred education model leads to retention of improved glycaemic control, QoL, responsibility distribution and reduced diabetes-related conflicts in the family.

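### Boundaries of the four Check your health burden categories are called arbitrary and left unfixed, and the categories are given no stated role beside the planned tests

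*Protocol article*

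**What the plan says.** All references are to the protocol article.

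**Measures and data collection.** Check your health covers physical health, emotional health, social relationships and general quality of life "on vertical thermometer scales, ranging from 0 to 100, with 0 indicating low perceived health and QoL". Each is rated twice, as it is and as it would be without diabetes. Burden is numerical: "The measured difference between, for example, physical health with and without diabetes is defined as the physical burden of diabetes". It is floored at one end: when "imagined physical health without diabetes is reported to be lower than with diabetes, the burden is interpreted as zero". The grading rule follows: "In this study, the marginal values for no burden, low burden, high burden or very high burden will be arbitrary".

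**Statistical analysis and power calculation.** The between-group method is stated once: "The differences between the groups will be analysed using an un-paired t-test with a 95% confidence interval and p < 0.05 considered as significant". Before-and-after comparisons use repeated measures ANOVA. The questionnaires inherit this: "When testing differences between groups using Disabkids, ‘Check your health’, DFCS and Swe-DES 23, the same statistical analysis will be used".

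**Where burden sits in the trial.** The hypothesis expects the negative burden of diabetes to fall, and the Discussion adds: "We also want to observe any changes in the burden of diabetes". Perceived health and quality of life are secondary outcomes. On the primary, the abstract is clear: "The primary outcome is haemoglobin A1c levels". Table 2 lists Check your health before pump start and at 6 and 12 months.

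**The concern.** A four-level grading invites statements such as a shift of patients from high to low burden. Any such statement depends on where the boundaries lie. The protocol does not merely omit the boundaries. It says they will be arbitrary, and gives no reason for any values and no time by which they are fixed. The statistical section does not close the gap, because it names the instrument, not the variable derived from it. A reader cannot tell whether the tested quantity is the raw thermometer score, the burden difference or the burden category.

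If boundaries were settled after follow-up scores were known and a category comparison were then reported with a p-value, its error rate would not be 5%. Burden is named in the hypothesis and is measured on four scales at two follow-up times, so there would be several openings for this.

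**Working it through.** **1. The plan's own figure.** The only computable figure is the HbA1c sample size. By the normal approximation, two-sided alpha 0.05 and 80% power:

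n = 2 × (1.960 + 0.842)² × (9.1 / 6)² = 2 × 7.849 × 2.300 = 36.1, rounded up to 37 per group.

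This reproduces the stated 37. Burden does not enter the formula, so nothing below changes it.

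**2. What the text settles and what it leaves open.**

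| Question | Answer in the protocol |
|---|---|
| Is burden numerical? | Yes, a difference of two 0-100 ratings, floored at zero |
| Are the category boundaries given? | No; described as arbitrary |
| When are they set? | Not stated |
| Which test applies to the instrument? | Unpaired t-test; repeated measures ANOVA |
| Which derived variable is tested? | Not stated |
| Is a test on the categories planned? | No |
| Are the categories descriptive only? | Not stated |

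**3. What a data-driven choice would do.** The documents give no distribution for burden, so its mean, SD and the candidate boundaries are assumptions. The simulation used 20,000 runs per scenario, 37 independent participants per group, no true effect and normal burden floored at zero. Single cuts were compared by a two-proportion z-test, and four-category sets by a t-test on category scores 0 to 3.

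| Procedure | Assumed mean, SD | Rejections at nominal 5% |
|---|---|---|
| t-test on the burden score | 15, 20 | 4.8% |
| One four-category set fixed in advance | 15, 20 | 4.8% |
| Best of 8 four-category sets | 15, 20 | 10.7% |
| Best of 3 single cuts (5, 15, 30) | 15, 18 | 11.8% |
| Best of 5 single cuts (5, 10, 20, 30, 40) | 15, 18 | 17.4% |
| Best of 7 single cuts (5, 10, 15, 20, 25, 30, 40) | 15, 20 | 19.6% |

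Varying the mean from 10 to 25 and the SD from 15 to 20 moved the best-of rows by no more than about two percentage points. The excess therefore comes from the choosing, and depends little on the assumed distribution. Each rate is for one scale at one time point.

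**4. Does grading lose information?** With an assumed downward shift of 13.2 points (mean 15, SD 20 before flooring), power was:

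- burden score, t-test: 73%
- four fixed ordered categories, t-test on category scores: 73%
- single split at 20: 56%

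Four ordered categories lose almost nothing. A single split loses 73 − 56 = 17 percentage points, but the protocol describes no single split.

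**The case against.** The strongest reply is that the plan already analyses the number. The t-test and ANOVA suit a numerical score, the statistical section assigns them to Check your health by name, and nothing says that the categories replace the score. Not ruling out a test on categories is different from planning one. This stands. A reader might infer that the protocol throws away the information in a 0-100 scale, but the text does not support that. The only loss written into the derivation is the floor at zero, and four ordered categories would cost almost no power in any case.

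The second reply is that arbitrary may mean set by convention without validated thresholds, which would be an honest disclosure. The sentence says nothing about timing. This also stands: a reader might infer that the investigators intend to choose boundaries after seeing the data, but the text permits this without announcing it. The error rates above describe a procedure that the protocol leaves possible, and do not describe its stated analysis.

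A third reply is that a condensed article may leave thresholds to a fuller document. This holds only in part. Unstated values alone would be no finding, but here the article states a rule for them, and a later document with justified boundaries would depart from that rule. The Discussion's interest in changes in burden does not mention categories, so it shows that burden matters but does not show that the categories will be tested.

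**Conclusion.** The point holds in a limited form. The boundaries are declared arbitrary, their values and timing are not fixed, and neither the numerical burden difference nor the descriptive role of the categories is named in the analysis section. The stated t-test on a numerical score keeps its nominal level (4.8% in simulation), and so does a four-category set fixed in advance (4.8%). Inflation, to about 11% for the best of eight four-category sets or 12-20% for the best of three to seven single cuts, requires two further steps that the protocol does not state: choosing boundaries after seeing scores, and testing on them.

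These figures rest on assumed distributions and candidate boundaries, and on independent participants. Randomisation here is by group, which is a separate matter that the simulation does not address. The instrument is secondary, and neither the HbA1c analysis nor the 37 per group is touched. Severity is minor; this is a free improvement.

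**What to change.** In Statistical analysis and power calculation, add a sentence to this effect: *Between-arm inference on burden uses the numerical burden score for each of the four Check your health scales, adjusted for its baseline value.*

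In Measures and data collection, replace the statement that the boundaries will be arbitrary with actual boundaries, fixed in writing before any follow-up data are opened and used for description only, without tests. Alternatively, drop the four categories.

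The baseline adjustment does not cure the boundary problem. It is a separate gain over the unpaired t-test that needs no new data, because Table 2 already collects the instrument before pump start. As an approximation, if baseline and follow-up burden correlate at r, residual variance is multiplied by 1 − r². For assumed r of 0.3, 0.5 and 0.7 this is 1 − 0.09 = 0.91, 1 − 0.25 = 0.75 and 1 − 0.49 = 0.51.

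The cost is one or two sentences and the freedom to regrade burden later. No extra participants, visits or measurements are needed.

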### Statistical analysis and power calculation

To detect a difference of 6 mmol/mol in HbA1c (SD: ± 9.1), at least 37 participants are required in each group (power 80% and alpha 0.05). SD is calculated from the available participants in the actual clinics (n = 160) at study start, mean HbA1c: 74.2 ± 9.1 mmol/mol. Allowing for patient withdrawals and those lost to follow up, 80 patients will be included in the study. All analysis will be conducted on an intention-to-treat basis. The differences between the groups will be analysed using an un-paired t-test with a 95% confidence interval and p < 0.05 considered as significant. A repeated measures ANOVA will be used for before and after comparisons in the groups, using the same confidence interval and level of significance. When testing differences between groups using Disabkids, ‘Check your health’, DFCS and Swe-DES 23, the same statistical analysis will be used.

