### GSD-Young

Self-management is an active and proactive process that involves activities and goals and that is continuously ongoing. It involves shared but shifting responsibility for diabetes care and decision making between the child and their parents, and it is a process that also involves health care staff. It is important to be aware that self-management may differ from one parent/child dyad to another [28]. Person-centred care highlights the importance of knowing the person behind the patient to engage the person as an active partner in his/her own care and treatment [29]. Guided self-determination (GSD) is an empowerment-based, person-centred, reflection and problem solving method intended to guide the patient to becoming self-determined and developing life skills to manage difficulties in diabetes self-management using worksheets. GSD helps the patient and the health care staff to overcome barriers to empowerment. It has been effective both in individual and group training of adults with type 1 diabetes [30]. [name] et al. have adapted GSD for adolescents and their parents as Guided self-determination-Young (GSD-Y) and there is an ongoing study of adolescents with type 1 diabetes in Denmark [31]. This study will evaluate the effect of an intervention using GSD-Y in groups of adolescents and their parents. It will be carried out at routine outpatient clinics.

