### Randomization

Adolescents and their parents who are willing to participate in the study will be divided consecutively into groups depending on which pump model they have chosen. The groups will then be randomized to either intervention or control. The main reason for group randomization is to make the study feasible within a reasonable time. It is not possible to provide enough staff to start different pump models at the same time. Our experience indicates that there are no differences in distribution between the sexes among those starting CSII; therefore, we have not stratified for gender.

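### The 80% power with 37 per arm assumes individually randomised adolescents, but the trial randomises groups; the power should be restated for that design

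*Protocol article*

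**What the plan says.** Two sections of the protocol article bear on this.

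- **Randomization.** Families who agree to take part "will be divided consecutively into groups depending on which pump model they have chosen". Then: "The groups will then be randomized to either intervention or control". The section calls this group randomisation and gives a practical reason: "The main reason for group randomization is to make the study feasible within a reasonable time".
- **Statistical analysis and power calculation.** The target is set out as "To detect a difference of 6 mmol/mol in HbA1c (SD: ± 9.1"), for which "at least 37 participants are required in each group (power 80% and alpha 0.05"). On the SD: "SD is calculated from the available participants in the actual clinics (n = 160) at study start". On the total: "Allowing for patient withdrawals and those lost to follow up, 80 patients will be included in the study". The between-arm comparison is an unpaired t-test.

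The power paragraph mentions no group size, number of groups, ICC or design effect. The GSD-Young section adds that the intervention itself is delivered to groups: "This study will evaluate the effect of an intervention using GSD-Y in groups of adolescents and their parents".

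**The concern.** The unit of randomisation is the group, while the sample size treats each adolescent as an independent observation. Members of a group share a pump model and a start period and, in the intervention arm, the same sessions with the same nurses. Their HbA1c values may therefore be correlated. If so, 74 adolescents carry less information than 74 independent ones. A valid test also has to draw its degrees of freedom from the fairly small number of groups.

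HbA1c is the primary outcome. If the stated power is taken at face value, a null result would be read as evidence, at 80% power, against a 6 mmol/mol effect. The design may not support that reading.

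**Working it through.** **Inputs from the article:** difference δ = 6 mmol/mol; SD σ = 9.1; 37 per arm; power 80%; α = 0.05 (two-sided reproduces the figure; one-sided would give 29); 80 enrolled.

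**Assumptions, not in the article:** equal groups of size m = 4 to 8; one ICC for both arms, 0.01 to 0.10; σ = 9.1 taken as the total SD.

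**1. Reproduce the stated figure.** n = 2 × (1.960 + 0.842)² × 9.1² / 6² = 36.1, rounded up to 37. Exact-t power at 37 per arm (72 df) is 79.9%; the normal approximation gives 80.9%. The stated figure is the independent-individuals figure, with design effect 1.

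**2. Design effect.** DE = 1 + (m − 1) × ICC, and the noncentrality is δ / (σ√(2·DE/37)). Example for m = 5, ICC 0.05: DE = 1.20; effective n = 37/1.20 = 30.8 per arm; noncentrality = 6 / (9.1 × √(2.4/37)) = 2.59. Power is 72.4% with 72 df.

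**3. Degrees of freedom from the groups.** With 74/m groups, df = 74/m − 2. In the example df = 12.8 and power is 66.7%. Fractional df arise because 74 does not divide evenly by every m.

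Power at 74 analysed is shown below as design effect only / with df = groups − 2.

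| m | ICC 0 | ICC 0.01 | ICC 0.05 | ICC 0.10 |
|---|---|---|---|---|
| 4 | 79.9 / 76.1% | 78.7 / 74.8% | 74.2 / 70.1% | 68.9 / 64.8% |
| 5 | 79.9 / 74.5% | 78.3 / 72.8% | 72.4 / 66.7% | 65.7 / 60.1% |
| 6 | 79.9 / 72.8% | 78.0 / 70.7% | 70.6 / 63.2% | 62.7 / 55.5% |
| 8 | 79.9 / 68.8% | 77.2 / 65.9% | 67.3 / 56.1% | 57.4 / 47.1% |

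The ICC 0 column isolates the df effect, which alone gives 69–76%.

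**4. If all 80 are retained (40 per arm).** Design effect only: 80.4–81.8% at ICC 0.01 and 71–78% at ICC 0.05. With group-based df: 70.5–78.5% and 60.6–73.9%.

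**5. Requirement by design effect alone.** 37 × DE runs from 37 × 1.15 = 42.6, so 43 (m = 4, ICC 0.05), to 37 × 1.70 = 62.9, so 63 per arm (m = 8, ICC 0.10).

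**6. The planned unpaired t-test (normal approximation).** It ignores the groups, so its statistic has variance DE instead of 1. Type I error is 2 × [1 − Φ(1.96/√DE)]: 6.8% (m = 4) to 9.2% (m = 8) at ICC 0.05, and 8.6% to 13.3% at ICC 0.10. Its rejection rate at δ = 6 is Φ((2.836 − 1.96)/√DE), where 2.836 = 6/(9.1√(2/37)). That is 79% at m = 5, ICC 0.05, and 75% at m = 8, ICC 0.10.

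**7. Baseline adjustment.** Residual SD = 9.1√(1 − r²), where r is the assumed correlation between baseline and follow-up HbA1c: 8.68, 7.88 and 7.28 for r = 0.3, 0.5 and 0.6. At 74 analysed with group-based df:

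- m = 5, ICC 0.05: 71%, 79% and 85% for r = 0.3, 0.5 and 0.6.
- m = 5, ICC 0.10: 72% and 79% for r = 0.5 and 0.6.
- m = 8, ICC 0.10: 58% and 65% for r = 0.5 and 0.6.

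**The case against.** The strongest reply has four parts.

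**Nothing is miscalculated, and a condensed article may leave detail to another document.** The first half is right: 37 is correct for the model used. A reader might infer an arithmetic slip, and there is none. The fault is an independence assumption that conflicts with the Randomization section. The second half does not help. The article gives difference, SD, α, power and n in full, and together they match the independent-individuals calculation without any allowance for groups.

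**The ICC is unknown and may be small.** This stands as to size. At ICC 0.01 the design effect costs only about 1 to 3 points at 74 analysed, and power stays at or above 80% if all 80 are retained. It does not stand as to direction, since 37 has no slack. The article gives no ground for assuming an ICC of zero.

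**The lower figures merge two penalties.** This stands. At m = 5, ICC 0.01, power is 78.3% from the design effect and 72.8% after the df change, so most of that loss is degrees of freedom. The two are therefore shown separately.

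**The df penalty belongs to an analysis that is not planned.** True, and under the planned t-test the rejection rate stays fairly close to nominal. It does so only because the test no longer holds its 5% level, so it cannot count as 80% power at α = 0.05. Any separate criticism of the unpaired t-test overlaps with this one and should not be counted twice.

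**Conclusion.** The point holds as a mismatch between the sample size and the unit of randomisation. The stated 80% belongs to an individually randomised trial. Under an analysis that respects the groups, 37 per arm falls below it for any positive ICC. The direction is firm; the size is conditional on group size and ICC.

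Two stronger readings are tempting, and the article supports neither.

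- **That the true power is some particular low value, such as 47% or 60%.** These are sensitivity results at ICC 0.10 with the df penalty included, not estimates for this trial.
- **That baseline adjustment makes good the loss with no extra patients.** That depends on r, which the article does not give, and all participants start pump treatment between the baseline and follow-up measurements. At m = 5, ICC 0.05, 80% is passed at r = 0.6 but narrowly missed at r = 0.5. At ICC 0.10 with m = 5 or m = 8 it is missed at both.

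**What to change.** Rewrite the power paragraph for the group-randomised design. It should give:

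- the expected number and size of groups;
- an assumed ICC with a range, including a low value;
- the power, or the detectable difference, for 74 to 80 adolescents under a group-level analysis with small-sample degrees of freedom;
- the dropout allowance kept apart from any allowance for clustering.

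Because baseline HbA1c is already collected, the calculation may use the baseline-adjusted residual SD, provided that the same adjustment is in the analysis. The gain should be shown over a range of correlations, for example 0.3 to 0.6, and not for one favourable value.

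The cost is one paragraph and, most likely, a less favourable stated power. Whether 80 adolescents suffice can be judged only once group size, ICC and correlation have been put forward. If they do not, the choice is between enrolling more and stating openly the larger difference that the trial can detect.

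### Intention-to-treat is promised for every analysis and losses are expected, but the two named tests would by default use observed cases only, on different subsets

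*Protocol article*

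**What the plan says.** All the relevant statements are in the protocol article, section Statistical analysis and power calculation.

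- Analysis principle: "All analysis will be conducted on an intention-to-treat basis".
- Expected losses: "Allowing for patient withdrawals and those lost to follow up, 80 patients will be included in the study". No loss rate is given.
- Between-group test: "The differences between the groups will be analysed using an un-paired t-test with a 95% confidence interval and p < 0.05 considered as significant".
- Before-and-after test: "A repeated measures ANOVA will be used for before and after comparisons in the groups, using the same confidence interval and level of significance".
- Questionnaires: for Disabkids, 'Check your health' and the other two scales ("DFCS and Swe-DES 23, the same statistical analysis will be used").

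The Abstract and Table 2 place the outcome measurements at baseline, 6 months and 12 months. The article is silent on how missing outcomes are handled. It does not say that adolescents with missing values are excluded.

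**The concern.** An unpaired t-test needs an outcome value from each person in it. A classical repeated measures ANOVA needs a complete set of values from each person, so one missed visit also discards the values that person did provide. With losses expected, the default use of these tests gives an analysed set smaller than the randomised set, and not the same set for the two tests. That sits badly with a promise covering all analyses.

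At stake are some precision, consistency between the between-group and the before-and-after results, and protection against selective loss. The Discussion stresses that adolescents with many diabetes-related conflicts, who tend to have poorer glycaemic control, should be represented in the sample. If such adolescents are also more likely to miss follow-up, which is plausible but not stated, observed-case results would under-represent them. If the loss differs by arm, the group comparison would shift.

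**Working it through.** **1. The plan's own sample size.** Inputs from the article: difference 6 mmol/mol, SD 9.1, "power 80% and alpha 0.05". A two-sided test is assumed.

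n per group = 2 × [9.1 × (1.960 + 0.842) / 6]² = 36.1, rounded up to 37. The t-based calculation gives 37.09. A one-sided test would give 29, so the stated 37 is two-sided. The figure reproduces.

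**2. The margin for losses.** 80 − 2 × 37 = 6, and 6/80 = 7.5%.

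**3. Who each test leaves out by default.** The ANOVA is taken to span all three measurement times.

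| Adolescent has values at | 12-month t-test | Three-visit ANOVA |
|---|---|---|
| baseline, 6 and 12 months | in | in |
| baseline and 12 months | in | out |
| baseline and 6 months | out | out |
| baseline only | out | out |

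The two tests differ in the second row. For a 6-month t-test they differ in the third row instead.

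**4. Size of the loss.** Let p be the proportion missing each follow-up visit. The article gives no rate, so p = 5% and 10% are assumptions.

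- t-test at one time point: loss = p, that is 5-10%, or 4-8 of 80.
- ANOVA, same adolescents miss both visits: loss = p, again 5-10%, or 4-8 of 80.
- ANOVA, misses independent: loss = 1 − (1 − p)². For p = 5%, 1 − 0.95² = 9.8%, leaving about 72 of 80. For p = 10%, 1 − 0.90² = 19%, leaving about 65 of 80. That is a loss of about 8-15 of 80.

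Permanent withdrawal pushes towards the second case and sporadic missed visits towards the third.

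**5. Power of the t-test on observed cases.** This starts from 40 per group, with the design difference and SD and without any allowance for group randomisation.

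| Analysed per group | Loss | Power, normal approximation | Power, t |
|---|---|---|---|
| 40 | 0% | 83.9% | 83.0% |
| 37 | 7.5% | 80.9% | 79.9% |
| 36 | 10% | 79.9% | 78.8% |
| 34 | 15% | 77.6% | 76.4% |

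**6. Illustration of bias.** If a fraction d of an arm is missing and those adolescents would have had HbA1c higher by g than the observed ones, the observed mean is too low by d × g. The bias in the group difference is then g × (d₁ − d₂). With assumed losses of 10% and 5% and g = 10 mmol/mol, this is 10 × 0.05 = 0.5 mmol/mol. That is 0.5/6, or about 8%, of the design difference, in favour of the arm that loses more. With equal loss and equal g in both arms it is zero.

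**The case against.** The strongest reply is that this is an omission in a condensed article. Rules for missing data commonly sit in the analysis plan, which is not shown. Either test can follow imputation. Intention-to-treat also means analysing people in the group to which they were allocated, and a t-test by allocated group respects that. All of this stands. The absence of an imputation rule is not the finding, and a reader who infers that the article declares a complete-case analysis goes beyond its text.

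Three other readings are tempting and should not be made.

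- That anyone who misses a visit leaves the randomised comparison. The ANOVA is assigned to before-and-after comparisons, while group differences go to the t-test. An adolescent who misses 6 months but attends 12 months stays in a 12-month t-test.
- That enrolling 80 to secure 74 proves a completer analysis set. Enrolment is commonly inflated for attrition whatever the analysis, because a lost participant carries less information.
- That the intervention arm carries seven extra sessions and so must lose more. According to the Intervention section, three of the seven fall at pump start, when both arms receive standard training, and all end within 4 months. The number of extra attendances is not established.

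It is also fair that a mixed model gains little for adolescents with no follow-up value, and that it does not remove bias if they do worse for reasons not captured in the data.

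What remains is that the article does commit to specific tests, and that these fit poorly with three-visit data, expected losses and the stated principle. A better-fitting method is available from the data already planned.

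**Conclusion.** The point holds as a mismatch between the stated principle and the default behaviour of the named tests. It is not a contradiction in the text, and no stated figure is wrong on this point.

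Its size is moderate. At an assumed 5-10% missing per follow-up visit, the between-group test loses 5-10% of adolescents. The before-and-after analysis loses between 5-10% and 10-19%, depending on whether the same adolescents miss both visits. At the 7.5% loss implied by the enrolment margin, power stays at about 80%, as designed. The bias illustration of 0.5 mmol/mol rests entirely on assumed loss rates and an assumed HbA1c gap, and it shows only that the effect would be small against 6 mmol/mol. The change is worth making because it is cheap and brings the analysis closer to the intention-to-treat statement.

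**What to change.** Replace the t-test and the ANOVA with one likelihood-based linear mixed model for HbA1c, and the same form for the questionnaire scores:

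- all available 6- and 12-month values from all randomised adolescents, analysed by allocated group;
- group-by-time effects, so that one model gives the between-group difference at each time point and the within-group changes on the same set of adolescents;
- baseline either adjusted for as a covariate or included as an outcome. Only the second lets adolescents with a baseline value alone contribute;
- a random effect for the randomised training group, since the Randomization section allocates groups formed by pump model and not individuals.

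State that the model relies on missing at random. Add one sensitivity analysis in which missing values are set worse than predicted, by an amount fixed in advance. Say in one sentence what intention-to-treat means here for adolescents without an outcome.

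The cost is a change of analysis wording, slightly more analysis work and an explicit missing-at-random assumption. No data beyond those in Table 2 are needed, and the sample size calculation need not change on this account.
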